## Materials and methods

### Football nurse intervention

The purpose of this study will be to evaluate the effect on teams’ sports medicine practice of randomising women’s football teams to a trained general nurse as a pitch side responder or usual practice. This study will be a cluster randomised control trial, whose reporting will follow the Consolidated Standards of Reporting Trials (CONSORT) 2010 statement: extension to cluster randomised trials [34]. Clusters will be registered teams in the Women’s Football League (24 teams) in Malawi. A 1x1 factorial design will be used to assess the effect of the FIFA Football Nurse intervention. The two allocated groups will be the football teams’ (clusters) sport medicine practice. The teams will be randomly assigned to intervention or control. Prior to the commencement of the intervention, a survey will be sent out to the women’s football teams to explore the current state of healthcare provision and policies for management or referral of players with injuries or illnesses, knowledge of injury prevention programs as well as their present medical needs. Following this, a cohort of 12 general nurses will receive a one (1) day training in basic football medicine using the latest version of the FIFA Emergency Care training manual. This training will be conducted by experienced sports medicine personnel as well as experienced trainers in basic life support (BLS) and first aid from the Departments of Emergency and Orthopaedics at Kamuzu University of Health Science (KUHeS), Blantyre, Malawi. Following the training, the nurses will be attached to a total of 12 women’s football teams during one competitive season. They will also be given access to reference materials that are adapted from the FIFA Emergency Care manual.

The roles of the nurses within the teams will include menstrual, basic health, injury risk assessment, nutritional, and mental health assessment; on field assessment, basic life support; immediate care, and referral of injuries; as well as maintaining records of injuries, illnesses, medication use and football exposure using standardised instruments as previously used in other studies [35, 36].

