### Trial design and study arms

#### Trial design

This study will be a cluster randomised controlled trial. This design is applicable as it allows for a field-based intervention to be implemented for one competitive season while decreasing the chances of contamination between the groups. African women’s football is the sport that has been chosen as it is the most commonly played women’s team sport on the continent and therefore, is a priority sport for improving medical care at and from grassroots levels. Adherence to the FIFA Football Nurse program; football exposure data; injury, illness and medication use surveillance and the in this trial will be similar to those used in previous football studies [35, 37] and conform with the definitions and data collection procedures outlined in the latest injury consensus statements [36]. The study will also include a qualitative evaluation of the participants’ (players, coaches, nurses) experience of the FIFA football nurse program.

All the 24 women’s teams in the Malawi Women’s Super league will be randomly assigned in a 1:1 ratio to either the Football Nurse intervention (INT–12 teams) or the control group/standard care (CON–12 teams) through a random draw. For the allocation schedule for random assignment to each arm, the names of the 24 teams will be placed in three (3) bowls, a bowl for each region. They will then be picked consecutively and alternately, and allocated into the INT and CON groups by one of the investigators ([name]). This will be done after the training of the nurses and after each team (cluster) have agreed to be a part of the study. For transparency, the random draw will be conducted in the presence of representatives from the football association and will be video and audio- recorded.

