*Mental health assessment*. This will be assessed using the Sports Mental Health Assessment Screening Tool-1 (SMART-1). The SMART-1 is a standardised assessment tool that aims to identify individual athletes potentially at risk for or already experiencing mental health symptoms and disorders to facilitate timely referral for those in need of support or treatment [42].

*Football exposure*: *Injury*, *illness*, *and medication use surveillance*. These data will be collected at a cluster level using injury, illness and football load forms as recommended in injury consensus statements [36]. The research team will follow up with each football nurse on a weekly basis to ensure surveillance data is being captured. Should an injury occur that requires investigations or further management, the nurses will refer to the PT/Dr, who will proceed with the treatment, design/prescribe further management and document accordingly. League performance will also be collated from FAM at the end of the season as this has previously been associated with injury rates in other team sports [43].

Assessment of injury behaviours, team medical practice, injury risk, nutritional data, and mental health assessment will be done at three time points: at the beginning before the trial begins, halfway through the trial, and at the end of the season. Football exposure and surveillance data will be collected and collated at the end of each training session and/or match until the end of the season.

*Measurement of potential confounders*. Despite all players playing in the same league and at the same level, primary confounders for injury risk include physical/ anthropometric characteristics; existing mental health or psychiatric conditions and home environment, which may influence the SMHAT- 1 values, for example. Secondary confounders include playing experience, playing position, and playing level as well as socio-economic status, which will affect nutrition, menstrual hygiene management and private management of injuries. Where possible, these will be considered in the analyses. Some of them will also be explored further in the qualitative interviews at closure of the protocol.

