*Patient and public involvement*. Patients and the public were not involved in the design of this protocol. However, various stakeholders in Malawi women’s football (e.g., nurses, women football players, district sports officers, district representatives in women’s football) will be consulted on the conduct, reporting, and dissemination plans for the research.

*Project time frame*. This project will be performed over an 8-month period during the 2022/2023 football season (May to December).

May 2022 –training of nurses; recruitment of football teams; randomisation of teams.June 2022 –baseline testing of teams (assessment of injury behaviours, team medical practice, injury risk, nutritional data, and mental health assessment)June 2022 to December 2022 –implementation of the football nurse intervention; injury surveillance; adherence and exposure data collection.October 2022 –midway testing of teams (assessment of injury behaviours, team medical practice, injury risk, nutritional data, and mental health assessment)December 2022 –final testing of teams (assessment of injury behaviours, team medical practice, injury risk, nutritional data, and mental health assessment); semi-structured interviews with sample of players and coaches from both groups and all nurses

*Outcomes and significance*. We expect to develop a low cost, sustainable and context relevant solution to manage the treatment gap of football injuries/illnesses in underserved communities such as women’s football. Through the study, we also anticipate the development and maintenance of player health, injury and illness monitoring databases for Malawian women football players in club football, which can be replicated in grassroots women’s football leagues in LMICs. This will allow the monitoring of trends and development of relevant preventive or management strategies in these settings. Additionally, we expect this study to lead to the development of a flagship model which can inform implementation of similar task sharing approaches to SEM practice in other LMICs in Africa and globally.

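### The timetable draws teams in May and takes baseline in June, so baseline is post-randomisation and conflicts with the stated assessment timing; secondary and sensitivity analyses are exposed

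*Protocol article*

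**What the plan says.** All references are to the protocol article.

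- **Project time frame.** May 2022: "training of nurses; recruitment of football teams; randomisation of teams". June 2022: "baseline testing of teams (assessment of injury behaviours, team medical practice, injury risk, nutritional data, and mental health assessment". June to December 2022: "implementation of the football nurse intervention; injury surveillance; adherence and exposure data collection".
- **Secondary outcome measures.** The same five assessments are made "at three time points: at the beginning before the trial begins, halfway through the trial, and at the end of the season".
- **Football nurse intervention (Materials and methods).** "Prior to the commencement of the intervention, a survey will be sent out to the women’s football teams"; nurse training comes after that survey.
- **Trial design.** Of the draw: "This will be done after the training of the nurses and after each team (cluster) have agreed to be a part of the study".
- **Blinding, Primary outcome measure, Secondary outcome measures.** Intervention teams cannot be blinded. Team practice and injury-prevention behaviour are both measured by self-administered questionnaire.
- **Standardisation of procedures.** The attached nurse has main responsibility for data in intervention teams. In control teams the research team works through a designated team member. Training is one week before the season.
- **Data analysis.** Arms are compared at baseline on factors such as age, career length and injury risk. Test scores are analysed by arm over time, and behaviours by a model with arm and time. Adjustment for baseline team practice appears among the sensitivity analyses.

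**The concern.** A baseline protects a randomised comparison only if allocation cannot have influenced it. Here the dated plan puts the draw first and the baseline after it, in the month the intervention begins, while another section says these assessments come ahead of the trial. The conditions in which allocation can affect a baseline are present: intervention teams know they have a nurse, practice and behaviour are self-reported, and data collection runs through different people in the two arms. Three of the five June domains (injury risk, nutrition, mental health) are also among the nurse's listed assessment roles.

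If June values already carry some effect of allocation, adjusting for them removes part of that effect, the arm-by-time contrasts start from a distorted point, and the baseline check on injury risk no longer tests only the outcome of the draw.

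**Working it through.** The plan gives no figure for this point, so the check is mainly of the order of events.

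**1. The order each section gives**

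- Project time frame: training, recruitment and draw (May); then baseline (June), with intervention from June.
- Secondary outcome measures: baseline, then trial.
- Football nurse intervention: survey, then nurse training.
- Trial design: nurse training, then draw.

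**2. Which conflicts are firm**

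- Project time frame against Secondary outcome measures: the natural reading is that a trial has begun once its clusters are randomised. On that reading June testing is not ahead of the trial.
- Trial design against Project time frame: no conflict. Both put the draw after nurse training.
- Football nurse intervention against Project time frame: conditional. Its survey has no entry in the timetable. If the survey is the June team-practice questionnaire, the two orders clash. If it is separate, the plan does not say how it relates to the June baseline. Either way this needs stating.

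**3. What is certain and what is not**

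On the timetable, baseline follows randomisation. It is not established that it follows the nurse's arrival: both fall in June, and testing could come first. Nor is it stated that the nurse collects the baseline; that is an inference from her general data-collection role.

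**4. Which analyses use the June values**

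- Baseline comparability: of the factors named, age and career length cannot be changed by allocation; injury risk could be.
- Over-time analyses (the mixed ANOVA for test scores, the arm-and-time model for behaviours): exposed.
- Sensitivity adjustment for baseline team practice: exposed.
- Primary comparison: no baseline covariate is named, and an unadjusted comparison of end-of-season cluster means does not use June values.

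**5. Illustration of size (assumptions, not estimates)**

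Take the planned effect of 0.19 from Sample size. Let *f* be the fraction of it already present in June, and *b* the slope of end-of-season score on baseline. Neither is in the document. The adjusted effect is 0.19 − *b* × (*f* × 0.19) = 0.19 × (1 − *bf*).

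- *f* = 0: 0.19, no bias.
- *f* = 0.10: 0.19 × (1 − 0.03) = 0.184 at *b* = 0.3; 0.19 × (1 − 0.07) = 0.177 at *b* = 0.7.
- *f* = 0.25: 0.19 × (1 − 0.075) = 0.176; 0.19 × (1 − 0.175) = 0.157.
- *f* = 0.50: 0.19 × (1 − 0.15) = 0.162; 0.19 × (1 − 0.35) = 0.124.

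This applies only to the baseline-adjusted sensitivity analysis. A shift in the opposite direction would reverse the sign.

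**The case against.** The strongest reply is that the timetable lists baseline testing ahead of implementation, and that the trial's start in Secondary outcome measures may mean the start of implementation. Baseline would then precede the nurses, and the sections would be compatible. The schedule of enrolment and assessments is in Fig 3, which is not reproduced in the text available and may fix the order. This much stands: the document does not show nurses at work before baseline. It does not remove the May-then-June order. If Fig 3 puts baseline before allocation, it disagrees with the timetable.

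Several stronger readings are tempting but unsupported:

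- *The draw is public, so all teams know their arm by June.* The draw is recorded and witnessed by football association representatives. The text does not say teams attend, or when they are told. Equally, it does not say the result is withheld until baseline is complete.
- *The nurse collects the baseline in her team.* This is plausible from her general role but not stated, and the practice and behaviour questionnaires are self-administered.
- *Every section contradicts the timetable.* Trial design agrees with it, and the pre-intervention survey may be a separate needs survey.
- *The primary result is compromised.* No baseline covariate or change score is specified for it. A reader might take the unnamed second factor of the two-way ANOVA to be time, but the text does not say so.
- *The loss can be put at a definite percentage of the planned effect.* Any such figure rests wholly on assumed values, and zero is among the possibilities.

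**Conclusion.** The concern holds in limited form. The dated timetable makes baseline, including the primary outcome measure, post-randomisation, and this sits badly with the statement that these assessments precede the trial. With open allocation, self-report and different routes of data collection in the two arms, baseline values could already reflect allocation.

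The consequence is confined to the baseline check on injury risk, the over-time analyses of secondary outcomes and the sensitivity analysis adjusting for baseline team practice. The unadjusted end-of-season comparison of cluster means is not affected. The size of any bias cannot be derived from the document; the illustration runs from none to an adjusted effect of 0.124 against 0.19, solely according to what is assumed. The timetable should be corrected, but the point does not invalidate the main comparison. Confidence is high on the order of dates and lower on whether any bias would result.

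**What to change.** 1. Reconcile Football nurse intervention, Secondary outcome measures and Project time frame so that they give one order of events. State whether the pre-intervention survey is the scored team-practice questionnaire or a separate instrument.
2. Reorder the timetable so that the team medical practice questionnaire and the other self-administered baseline questionnaires are returned by all 24 teams before the draw.
3. Complete physical testing before any nurse is attached to a team.
4. If the draw has already been held, label June values post-randomisation and do not use them as a baseline covariate. Use the pre-intervention survey instead only if it contains the same scored instrument.

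**Cost.** Items 1 and 2 need no additional teams or measurements. The draw moves later. Training is planned one week before the season and the draw follows training, so the interval is short: a later draw has to be fitted around both, or training brought forward, if nurses are to be in place at the start. Item 3 may need extra staff time if the attached nurses were expected to carry out physical testing in their own teams.
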